**5. 5 Exclusion criteria**

Patients were excluded from the study

1. Subjects who had received an investigational medication, AchEIs, N-methyl-D-aspartate receptor antagonist, or anticholinergic drugs within 4 weeks prior to screening or
2. Subjects who had evidence of active skin lesions, allergy to the study drugs, or any advanced or unstable disease that would prevent completion of the study.
3. Subjects who had diseases precluding enrolment in the study included acute and severe asthmatic conditions, severe and unstable cardiovascular disease (bradycardia with heart rate < 50 bpm, sick sinus syndrome, sinoatrial block, or 2nd/3rd degree atrioventricular block), active peptic ulceration or gastrointestinal bleeding, severe hepatic or renal disease, malignancy within the past 5 years, or severely declined vision or hearing.
4. Subjects who had a history or presence of any contraindication for the application of AchEIs, a history of other concomitant neurodegenerative or psychiatric disease, a history of drug or alcohol addiction within the previous 10 years
5. Subjects who had severe ischemia based on the CREDOS WMH visual rating scale, and multiple large territorial infarctions or single strategically placed infarctions on MRI scan conducted at baseline or within the 12 months prior to the baseline examination.

**6. Intervention**

**6.1 Investigational drug**

Once a day, a patch size of 5 cm2 with a rivastigmine patch (containing 9 mg of rivastigmine and 4.5 mg delivered over 24 hours) and a once daily patch size of 10 cm2 rivastigmine patch 18 mg and 9.5 mg delivered over 24 hours) is administered as a therapeutic drug during the study period.

**6.2 Treatment regimen**

**6.2.1 Treatment schedule**

|  | Weeks 1-4 | Weeks 5-8 | Weeks 9-12 | Weeks 13-24 |
| --- | --- | --- | --- | --- |
| AD without white matter change | Patch 5 cm2 | Patch 10 cm2 | | |
|  |  | | |
| AD with white matter change | Patch 5 cm2 | Patch 10 cm2 | | |
|  | | | |

**6.2.2 Subject assignment and prescribing and administering medication**

Patient subjects will be allocated to AD without white matter change group or AD with white matter change group at the baseline. All patients start on a 5-cm2 patch and their dose is increased to a 10-cm2 patch after 4 weeks. White matter changes will be defined by CREDOS protocol. Periventricular white matter (PWM) changes are classified into P1 (caps or rim <5 mm), P2 (5 mm <caps or rim <10 mm), P3 (10 mm <caps or rim). Likewise, deep white matter (DWM) ischemic lesions are classified into D1 (the longest diameter of DWM lesion <10 mm), D2 (10mm<DWM<25mm), and D3 (25mm <DWM). The patients would be divided into two groups according to combinations of PWM and DWM ischemic lesions: Group I (without or minimal white matter changes: D1P1,) and Group II (mild to moderate white matter changes: D1P2, D2P1, D1-P3, D2-P2, D2-P3, D3-P1, D3-P2).

| **Treatment Arm** | **# of Patients Entered Treatment** | **Type of Study Drug** | **Compound** | **Min Dose** | **Max Dose** | **Frequency** | **Admin. Route** |
| --- | --- | --- | --- | --- | --- | --- | --- |
| AD without WMC | 200 | Exelon patch | Rivastgmine | 5cm2 | 10cm2 | qd | PO |
|  |  |  |  |  |  |
| AD with WMC | 100 | Exelon patch | Rivastgmine | 5cm2 | 10cm2 | qd | PO |
|  |  |  |  |  |  |

### 6.2.3 Controlling medication doses and suspending doses

If the subject is unable to tolerate the assigned dose, dose adjustment and suspension of dosing are allowed. The following treatment coordination schemes are recommended:

• In the case of a tolerability problem, the caregiver contacts the researcher as soon as possible.

• If the tolerability problem improves and subsequent days of treatment are less than 3 days, resume treatment to the same dose level as before administration. At this time, if tolerability is still a problem and the subject receives a patch of 5 cm², the subject may be dropped from the test. If tolerability is still a concern and the subject is treated with a 10 cm² patch, resume treatment at the lower dose level.

• If the tolerability problem improves and the days of consecutive administration are more than three days, resume treatment at a lower dose than before administration.

• If the subject's tolerability has improved, restart the dose titration schedule. If the tolerability problem is caused again at the next dose titration step, administration may be omitted again. Future attempts to titrate the dose will be at the discretion of the investigator (ie, if necessary for tolerance, the dosage does not necessarily have to be titrated to the target maximum dose).

• The dose level reduction required due to tolerability issues is permissible at any time during the treatment period.

### 6.2.4 Concomitant medication

All existing diseases or medical conditions are treated based on the prevailing medical practice.

The following treatments are not allowed after screening.

- All other clinical trial drugs
- Drugs or treatments known to cause major organ damage
- Rivastigmine capsule, donepezil, galantamine
- Muscle relaxant, general anesthesic medication
- Lithium
- Anticholinergic drugs (amantadine, atropine, benztropine, trihexyphenidyl)
- Tricyclic antidepressant
- Vitamine E, Estrogen, Gingko biloba, nootropics [ie. piracetam, Acetyl-L-carnitine, ergoloid mesylates, oxiracetam, Choline alphoscerate]

The following medications are allowed to be administered but with certain restrictions:

- - After screening, it is recommended that psychotropic drugs (antipsychotics, antidepressants, anxiolytics, anticonvulsants, sleeping pills) be discontinued or used with the minimum dose required for the patient's symptoms. If you cannot discontinue use, you can take part in this study if you are taking a mental agonist at a stable dose for a period of 4 weeks before baseline. Try to maintain this stable dose for the duration of the trial. All treatments initiated during the trial should be performed for the shortest possible period of time with the lowest effective dose.

The investigator will train the subject to inform the testing laboratory of all new drugs used since the start of the trial.

All drugs used after the subject started treatment with the test drug should be recorded in the Concomitant medications after start of study drug section of the CRF.

### 6.2.5 Discontinuation of trial drug treatment and early elimination of subjects

If the investigator believes that continuing the administration of the test drug will pose a significant safety risk to the subject, the subject should stop administering the test drug. In the following situations, the study medication may be discontinued according to the judgment of the investigator:

- If the investigator determines that treatment is discontinued due to abnormal or clinically significant changes in test results or abnormalities
- If the researcher determines that continuing treatment will be detrimental to the well-being of the subject

Subject to the following grounds, the subject is severely disqualified from the examination:

- Withdrawal of subject consent
- Stop taking the test drug for more than 8 days
- If the researcher determines that drop-out is best for the subject at any time for any reason

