### A violation of the plan does not lead to the elimination of the subject unless the risk is significant to the safety of the subject. The subject may voluntarily cease to participate in the trial at any time for any reason. Subjects, who are willing to discontinue participation, do not want to visit, or fail to follow-up for any other reason may be considered dropouts.

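### Sections 6.2.3 and 6.2.5 overlap unreconciled for drug interruptions of 9 days or more, and removal under 6.2.5 can put an early ADAS-Cog in place of the week-24 endpoint

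*Protocol*

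**What the plan says.** **Interruptions (protocol 6.2.3).** Dose adjustment and suspension are permitted when the assigned dose is not tolerated. The restart rules are introduced with "The following treatment coordination schemes are recommended". For the longer pause the rule is: "If the tolerability problem improves and the days of consecutive administration are more than three days, resume treatment at a lower dose than before administration". No maximum length is given. On a later recurrence, "If the tolerability problem is caused again at the next dose titration step, administration may be omitted again". Section 6.2.5 is not mentioned.

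**Removal (protocol 6.2.5).** One list sets out when the trial drug may be discontinued. A second list opens with "Subject to the following grounds, the subject is severely disqualified from the examination" and has three grounds: withdrawn consent, "Stop taking the test drug for more than 8 days", and the researcher's judgement that dropping out is best for the subject. No exception is made for a suspension that 6.2.3 permits.

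**Assessment after stopping early.** Section 6.2.6 says that subjects who discontinue treatment after baseline are assessed at week 24, and the treatment-visit paragraph of section 7 says much the same. The opening of section 7 says that subjects dropped after baseline, whatever the cause, are recalled promptly for all final-visit assessments. Table 1 heads Visit 5 as week 24 or early termination, and schedules ADAS-Cog only there and at Visit 2.

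**Analysis (protocol 8.1 and 8.3.1).** The primary outcome is change in ADAS-Cog from baseline to week 24. ITT and per-protocol analyses are planned, with missing values filled by LOCF.

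**The concern.** A patient who pauses the patch for tolerability, improves, and has been off drug for 9 days or more meets both the restart recommendation and the disqualification ground. Nothing says which prevails, so two sites can read the protocol carefully and treat the same patient differently.

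This reaches the primary endpoint because 6.2.5 removes the patient from the trial and not only from the drug. A patient who is kept supplies a week-24 ADAS-Cog. A patient who is removed may supply a score taken much earlier, or none after baseline. The study is open-label (section 1.2), and its groups are formed by white matter rating rather than by randomisation (section 6.2.2). Uneven handling between the groups would therefore be neither masked nor balanced by design.

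**Working it through.** No sample size, power or alpha figure bears on this point. The check sets the rules side by side.

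**Step 1: apply the day limits.** The inputs are two limits in 6.2.3 (the short branch, "subsequent days of treatment are less than 3 days, resume treatment to the same dose level as before administration", and the longer branch, more than three days) and one in 6.2.5 (more than 8 days). In both 6.2.3 branches the days are read as days off drug. That is an inference, because the text literally speaks of days of treatment or administration, but a restart rule makes little sense otherwise. More than 8 days means 9 whole days or more.

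| Whole days off drug | 6.2.3, once tolerability improves | 6.2.5 |
|---|---|---|
| 1–2 | restart, same dose level | not triggered |
| 3 | neither branch applies | not triggered |
| 4–8 | restart, lower dose | not triggered |
| 9 or more | restart, lower dose (no upper limit) | ground for disqualification |

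The overlap starts at day 9 and has no end. Exactly 3 days falls into a small gap of its own. Section 6.2.5 also does not say whether its days are consecutive or cumulative. Since 6.2.3 allows repeated omission, two pauses of 5 days (5 + 5 = 10) are unsettled too.

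**Step 2: follow one patient to the endpoint.** As an illustration only, suppose a pause starts on day 28, when section 6.2.2 has the patch size increased. Nine days off drug are complete on day 28 + 9 = 37. Week 24 is day 24 × 7 = 168.

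- Kept in the trial: ADAS-Cog at about day 168.
- Removed, and recalled promptly under the opening of section 7: ADAS-Cog soon after day 37, up to 168 − 37 = 131 days (about 18.7 weeks) early. Table 1 puts this score in the same column as week 24.
- Removed, with no recall visit achieved: the only earlier ADAS-Cog is baseline, so LOCF gives a change of baseline − baseline = 0.
- Removed, but handled as an early discontinuer under 6.2.6: ADAS-Cog at about day 168, off drug.

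One clinical course thus leads to different primary endpoint values, depending on which sentence the site follows.

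**Step 3: effect on the group comparison.** If a fraction p of a group is handled by early removal and each such patient's change score shifts by d on average, the group mean shifts by p × d. The between-group difference shifts by p₁d₁ − p₂d₂, where 1 and 2 index the two white matter groups. The shift vanishes when the products are equal and matters when they differ. The protocol gives neither p nor d for either group.

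**The case against.** **The two sections can be reconciled.** The 6.2.3 schemes are recommendations, conditional on improvement, and concern the dose at restart. Section 6.2.5 is worded as a disqualification. Read together, 6.2.5 can be the outer limit: restart up to day 8, removal after that. This stands as a possible reading, and it is why a reader should not infer that the rules are flatly opposed or that 6.2.3 obliges a restart. It does not close the gap. A site could equally take 6.2.3 as the specific rule for tolerability pauses and 6.2.5 as aimed at other stoppages, and the text chooses neither.

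**A third conflicting rule?** A reader might add the sentence after the 6.2.5 lists: "A violation of the plan does not lead to the elimination of the subject unless the risk is significant to the safety of the subject". It does not clearly apply. A pause that 6.2.3 permits is not obviously a violation, and the sentence may be meant for deviations outside the listed grounds.

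**Do sites decide retention because of this gap?** A reader might infer that. The third ground in 6.2.5 already gives the researcher wide discretion to drop a subject, so reconciling the 8-day wording would not remove it.

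**Are removed patients lost from the analysis?** The documents do not support that. Sections 6.2.6 and 7 provide a final assessment, and 8.1 plans ITT with LOCF. What is at risk is the timing of the score, and the drug exposure behind it, rather than the patient's place in the analysis.

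**Could an SAP settle it?** An SAP could say how an early score is used. It could not supply a week-24 score that was never taken because the visit rules conflict.

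**Conclusion.** The point holds as an unreconciled overlap with a consequence for the primary endpoint. From 9 whole days off drug, the restart recommendation and the disqualification ground both apply as worded, with no stated precedence. Because 6.2.5 turns an interruption alone into leaving the trial, and sections 6.2.6 and 7 give two timings for the assessment that follows, an early ADAS-Cog or a carried-forward baseline can replace the week-24 value.

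The size of the effect cannot be stated. A reader might set an assumed rate of long interruptions against the 20% drop-out allowance in section 5.3. No such rate is in the protocol, and these patients may already be counted in that allowance. Nor does the protocol show that tolerability differs between the white matter groups, so bias in the comparison is possible rather than demonstrated.

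The conclusion rests on one reading, that the day counts in 6.2.3 mean days off drug. The loss of week-24 timing after removal under 6.2.5 does not depend on that reading.

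**What to change.** 1. Reconcile 6.2.3 and 6.2.5 so that an interruption of a given length has one outcome at every site. State whether the 8-day ground covers a suspension that 6.2.3 permits, whether the days are consecutive or cumulative, and that the counts in 6.2.3 are days off drug, including the exactly 3-day case. Which clinical rule applies is for the sponsor to decide.
2. In 6.2.5, separate stopping the trial drug from leaving the trial. A patient who is off drug and has not withdrawn consent should still attend the scheduled week-24 assessment.
3. Align 6.2.6, both statements in section 7 and the Visit 5 heading of Table 1 on that timing.

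The cost is a short wording amendment, the review board approval that section 9 requires for protocol changes, and a notice to sites. No visits or patients are added, since the week-24 visit is already scheduled. The small downside is that more off-drug or reduced-dose patients contribute week-24 data to the ITT analysis.

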### A violation of the plan does not lead to the elimination of the subject unless the risk is significant to the safety of the subject. The subject may voluntarily cease to participate in the trial at any time for any reason. Subjects, who are willing to discontinue participation, do not want to visit, or fail to follow-up for any other reason may be considered dropouts.

### In the event of premature drop out, the investigator will assess the subject's primary cause of early withdrawal of the clinical trial and provide that information in the Study Completion section of the CRF. If the subject is unclear because he has not attended a clinical trial visit without expressing his intention to stop participating, the researcher should conduct a telephone conversation with the subject.

### 6.2.6 Termination of study

All subjects will receive a final final examination for efficacy and safety evaluation at the end of the 24-week treatment period. Subjects who discontinue treatment early after the baseline will be assessed at the end of the 24th week.

### 6.2.7 Early termination of study

Clinical trials may be terminated at any time at the discretion of the investigator meeting. If termination of the clinical trial is required, the subject will be interviewed and treated as soon as possible, as described for the 7 early withdrawal subjects. Additional procedures may be provided to the investigator to ensure that appropriate action is taken to protect the subject's interests. The investigator should report the early termination of the clinical trial to the IRB.

# 7 Study visit and assessment

We described all study visits schedule and assessment activities in table 1.

The subject will be present on all scheduled visits within 7 days from the specified date or 7 days prior to the specified date within 14 days. Subjects who have been dropped early in the test after the baseline for any reason will re-arrange their visit as soon as possible to perform all assessments scheduled at the final visit.

**Screening visit:** Subject / guardian consent, demographic and background information, inclusion and exclusion criteria, NINCDS-ADRDA 'probable' diagnostic criteria for Alzheimer's disease, current / past history, concurrent medication, vital signs, physical examination, height, weight, neurological examination, MMSE, and the screening confirmation.

**Baseline visit:** This visit will be conducted within 28 days of the screening visit.

The baseline assessment included concomitant medication, dose regimens, compliance, ADAS-cog, MMSE, FAB ADCS-ADL, CGA-NPI, CDR-SB, Mini-Zarit, vital sign, physical examination, .

**Treatment visits:** A safety assessment is carried out at each visit. Safety assessments include signs of vital signs, physical examination, weight, neurological examination, and adverse events. Therapeutic evaluations are performed at each visit and include concurrent medications, dose-related records. The efficacy assessment was performed at the end of 24 weeks and included ADAS-cog, MMSE, FAB, ADCS-ADL, CGA-NPI, CDR-SB and Mini-Zarit. Subjects who discontinue treatment early will be assessed at the end of treatment at the end of the 24th week.

**Unscheduled visits**: Perform an assessment related to the cause of the unscheduled visit.

Table 1. Study Process

| **Assessment and activities** | **Visit schedule** | | | | |
| --- | --- | --- | --- | --- | --- |
| **Visit 1** | **Visit 2** | **Visit 3** | **Visit 4** | **Visit 5** |
|  | **D-28~1** | **Day 0** | 4wk****7d | 12wk****7d | 24wk****7d, or  Early termination |
| Informed consent | X |  |  |  |  |
| Inclusion/Exclusion criteria | X |  |  |  |  |
| Medical history | X |  |  |  |  |
| NINCDS/ADRDA probable AD criteria | X |  |  |  |  |
| **Concomitant Medication** | | | | | |
| Concomitant medication | X | X | X | X | X |
| Drug dosage description | X | X |  | X |  |
| **Efficacy measure s** | | | | | |
| ADAS-cog (patient) |  | X |  |  | X |
| Caregiver burden(caregiver) |  | X |  |  | X |
| MMSE(patient) |  | X |  |  | X |
| ADCS-ADL (caregiver) |  | X |  |  | X |
| CGA-NPI (caregiver) |  | X |  |  | X |
| CDR-SB |  | X |  |  | X |
| **Safety measures** | | | | | |
| Vital sign | X | X |  | X | X |
| Heigt | X |  |  |  |  |
| Weight / Physical examination | X |  |  |  | X |
| Neurologic examination | X | X |  | X | X |
| Adverse events |  | X | X | X | X |
| Medication schedule | **screening** | **5cm2**  **patch** | **10cm2**  **patch** | | |

**7.1 Subject demographic and background information**

- Demographical data
- Vital sign: blood pressure,
- Weight, height
- Disease characteristics: NINCDS/ADRDA criteria for AD.
- Past and present medical history
- Family history and history for smoking and alcohol consumption

**7.2 Treatment exposure and compliance**

Enter the test drug dose prescribed to the subject in the Dosage Administration Record column with the start date, end date, dose, and reason for the dose adjustment.

Concomitant medications, including psychotropic drugs (antipsychotics, antidepressants, anxiolytics, anticonvulsants, sleeping pills) used in the treatment of emotions or behavior, are recorded in the CRF. Record the product name, start date, end date, and reason for use.

**7.3 Efficacy**

At the baseline and 24-week visits, the same evaluator takes charge of the same subject for the same examinations as possible.

- Alzheimer’s Disease Assessment Scale-Cognitive subscale (ADAS-cog)
- MMSE (Mini-Mental State Examination)
- Frontal Assessment Battery (FAB)
- Alzheimer’s Disease Cooperative Study - Activities of Daily Living (ADCS-ADL)
- Caregiver-Administered Neuropsychiatric Inventory (CGA-NPI)
- Clinical Dementia Rating Scale-Sum of Boxes (CDR-SB)
- Caregiver burden scale Korean version of mini-Zarit

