**1.2 Study design**

Investigator Initiative Trial, Multi-center, Prospective, Open-label

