In fact, one previous randomized trial has indicated that after rivastigmine treatment for 26 weeks, patients with AD with vascular risk factors (VRFs) had greater clinical benefit in cognition, activities of daily living, and disease severity than those with AD without VRFs. Another recent retrospective analysis of a large international 24-week multicenter randomized double-blind placebo-and active-controlled trial also indicates that VRF status seems to have a great impact on treatment response in AD. In these studies, however, VRFs were determined only using the Modified Hachinski Ischemic Score (HIS) or by assessing the presence or absence of reported VRFs at screening. It thus remains unknown whether patients with AD with VRFs had actual concurrent CVD pathology as assessed using brain magnetic resonance imaging (MRI). Furthermore, there have been no studies on the effects of rivastigmine patch in patients with AD with different degrees of WMH.

We thus investigated the efficacy of rivastigmine patch in patients with mild to moderate AD with minimal versus moderate ischemic WMHs. The treatment effect of rivastigmine is generally larger in patients with AD with VRF than in those with AD without VRF [15], and that VRFs are associated with greater WMHs or reduced white matter integrity [18,19]. We thus hypothesized that patients with AD with moderate WMHs will have greater clinical improvements from baseline than those with AD with minimal WMHs. To maximize the therapeutic effects of rivastigmine on cognitive function, we used a transdermal 9.5 mg/24hour rivastigmine patch (10cm2), which offers continuous delivery of the drug with minimal plasma fluctuations. This delivery method leads to potentially similar efficacy and fewer side effects compared to the highest dose of rivastigmine capsule.

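### Nothing keeps the CREDOS white-matter grade from the people who score ADAS-cog, although that grade is the trial's only contrast; the grade's printed cut-points also leave exact ties unassigned

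*Protocol*

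**What the plan says.** - **Design.** Protocol section 1.2 gives the whole design as "Investigator Initiative Trial, Multi-center, Prospective, Open-label". Sections 6.2.1 and 6.2.2 give both groups the same patch schedule, so the comparison is between MRI groups and not between treatments.
- **Hypothesis.** The background text before section 4 states a direction: "patients with AD with moderate WMHs will have greater clinical improvements from baseline than those with AD with minimal WMHs". Section 4.1 repeats it in substance.
- **Grouping.** Section 6.2.2: "Patient subjects will be allocated to AD without white matter change group or AD with white matter change group at the baseline". Periventricular classes are "P1 (caps or rim <5 mm), P2 (5 mm <caps or rim <10 mm), P3 (10 mm <caps or rim"; deep classes are "D1 (the longest diameter of DWM lesion <10 mm), D2 (10mm<DWM<25mm), and D3 (25mm <DWM". Group I is D1P1 alone. Group II is a list of seven other combinations. D3P3 is in neither list, and exclusion criterion 5 removes severe ischaemia on the CREDOS scale.
- **Scoring.** Section 7.3 has the only rule about evaluators: "the same evaluator takes charge of the same subject for the same examinations as possible". ADAS-cog is scored twice, at baseline and at week 24 (section 7, Table 1), and the primary outcome is the change between them (section 8.3.1).
- **Not stated.** The readable text does not say who grades the MRI, when the grade becomes final, or whether the evaluators may know it. The visit descriptions and Table 1 in section 7 list no grading step.

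**The concern.** In most open-label trials the assessor can hardly avoid knowing the arm, because the treatments differ. Here they do not differ. The evaluator can know that the patient wears a rivastigmine patch and still not know the white-matter group. Masking the grade is therefore available at almost no cost, and the protocol does not ask for it.

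The stake is the primary contrast. The groups are not randomised, the expected direction is written into the protocol, and the outcome is one difference between two scored assessments. If an evaluator who knows the grade scores week 24 a little more favourably in patients expected to improve, that shift goes straight into the between-group difference. A positive result could then not be separated from rater expectation.

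The cut-points are a second and smaller matter. The inequalities are strict on both sides, so a measurement exactly on a limit has no class, and for some patients that leaves the group undefined.

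**Working it through.** **1. The plan's own sample size.** Inputs from section 5.3: difference 2.3, SD 6.0, two-sided alpha 0.05, allocation 1:2. Power does not appear in the readable text (the formulas are figures that are not shown), so I assume 80%.

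n (with WMC) = (1 + 1/2) × (1.960 + 0.842)² × 6.0² / 2.3² = 1.5 × 7.85 × 36 / 5.29 = 80.1, rounded up to 81. The other group is 162 and the total 243, as stated. Power of 85% or 90% would give 276 or 324, so 80% is the value that fits.

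**2. Which rater bias matters.** Suppose knowledge of the grade adds b0 to the between-group difference at baseline and b24 at week 24. The difference in change scores is then biased by b24 − b0. If b24 = b0, the bias is zero. Only the shift b = b24 − b0 counts. (Section 8.1 uses ANCOVA with the baseline score as covariate. If week 24 has slope β on baseline, the bias is b24 − β·b0, so a constant bias c leaves c(1 − β) and cancels fully only when β = 1. The figures below use the simple change score, as section 5.3 does.)

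**3. Effect of a shift b on the false-positive rate, with no true difference.**

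SE = 6.0 × √(1/81 + 1/162) = 0.816.

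P(reject) = Φ(b/SE − 1.96) + Φ(−b/SE − 1.96).

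| Assumed shift b (points) | b/SE | Two-sided false-positive rate |
| --- | --- | --- |
| 0 | 0 | 5% |
| 0.25 | 0.31 | 6.1% |
| 0.5 | 0.61 | 9.4% |
| 1.0 | 1.22 | 23.2% |
| 1.5 | 1.84 | 45.1% |

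The shifts are assumptions; the protocol gives no basis for choosing one. For scale, 0.5 is 22% of the planned 2.3 points (0.5/2.3) and 1.0 is 43%.

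**4. Which cut-point ties matter.** I put each exact limit through the Group I and Group II lists of section 6.2.2.

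| Exact value | Neighbouring classes | Consequence |
| --- | --- | --- |
| Rim 5 mm | P1 / P2 | With D1: Group I or II. With D2 or D3: Group II either way |
| Deep lesion 10 mm | D1 / D2 | With P1: Group I or II. With P2 or P3: Group II either way |
| Rim 10 mm | P2 / P3 | With D3: Group II or neither. Otherwise Group II either way |
| Deep lesion 25 mm | D2 / D3 | With P3: Group II or neither. Otherwise Group II either way |

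Two of the four ties can move a patient between the compared groups. The other two matter only next to D3P3.

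**5. Direction of the tie effect.** Assume a share q of all patients sits on a deciding limit and is placed by coin flip, with one third truly in Group II. The share of true Group II patients is then (1/3)(1 − q/2) / [(1/3)(1 − q/2) + (2/3)(q/2)] in observed Group II, and (1/3)(q/2) divided by the remaining fraction in observed Group I. For q = 5% these are 0.951 and 0.013, so the expected contrast is 2.3 × (0.951 − 0.013) = 2.16. For q = 2%, 5% and 10% the contrast is 2.24, 2.16 and 2.02, and power at 81/162 is 78.4%, 75.3% and 69.7%, against 80.4% by the same normal approximation without ties. The contrast shrinks, which works against the hypothesis. The values of q are assumptions.

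**The case against.** **The same-evaluator rule is itself a safeguard.** It is. Keeping one evaluator per patient helps a stable bias to cancel, and nothing in that sentence is wrong. It does not address an expectation of improvement that acts at week 24, which is the part that survives.

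**The size is assumed.** True. No rater shift is documented, and a full point is a large share of the planned effect. The table shows how sensitive the test is; it does not predict a shift.

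**Masking could be left to another document.** Who may know the exposure during scoring is trial conduct and belongs with the assessment rules in section 7.3. An analysis plan cannot restore it afterwards.

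**The cut-points defer to CREDOS.** Section 6.2.2 says the CREDOS protocol defines the changes, and that source may settle ties and the severe class. Symbols can also be lost in text extraction: the visit-window sign in Table 1 is gone. On the other hand, the less-than-or-equal sign survives in inclusion criterion 6. This objection stands far enough to make the cut-points a clarification only.

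**What a reader might infer, and the documents do not support.** One could read the gaps as letting group assignment drift toward the hypothesis. Section 6.2.2 places allocation at baseline, before any week-24 score exists, and ties handled without regard to outcome dilute the contrast. A drift in favour would need regrading after outcomes are known, or selective placing of borderline patients. The protocol does not rule these out, but it does not show them. Nor does it say that borderline scans are resolved locally by someone who has seen the patient; it is silent on the reader.

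**Conclusion.** The point holds for scoring. In a non-randomised comparison with a declared direction, the protocol leaves the evaluator free to know the grade that defines the comparison, although the common patch schedule makes that knowledge unnecessary. An assumed grade-related shift of 0.5 points between baseline and week 24 takes the false-positive rate from 5% to about 9%, and 1.0 point to about 23%. These figures rest on SD 6.0, 81/162 evaluable patients, a simple comparison of change scores and no true difference. The trial can run without the change, but a positive primary result would be hard to defend.

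The cut-points are secondary. As printed, a 5 mm rim with D1 or a 10 mm deep lesion with P1 falls in neither group; a 10 mm rim and a 25 mm deep lesion matter only next to D3P3. The number of such ties is unknown, and so is the loss of power. No corrected sample size follows from either part.

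**What to change.** - **Section 7.3:** state that the existing evaluators of ADAS-cog, MMSE, FAB and CDR-SB are not told the CREDOS grade or the group, and name the role that holds this information.
- **CRF:** record the grade before the baseline ADAS-cog is scored.
- **Section 6.2.2:** make the P and D classes contiguous, with each limit assigned to one class following the CREDOS scale.

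The cost is wording and a handling instruction; no extra reader, visit or patient is needed. Where the evaluator also enrols the patient, another existing team member must hold the grade. Masking evaluators protects the caregiver-reported scales (ADCS-ADL, CGA-NPI and mini-Zarit) only in part, since the caregiver may know the MRI result.
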